### Standardized training for delirium assessors

2.10

All study team members performing delirium assessments will undergo a rigorous, standardized training process. Three psychiatrists will train the delirium assessors before the start of the study. The training is divided into three parts: the exercise of theoretical knowledge of delirium, simulation training to perform delirium assessments, and an examination. Training in the theoretical understanding of delirium includes the definition, clinical manifestations, and classification of delirium, delirium evaluation tools (3D-CAM and CAM-S), and the differential diagnosis of delirium. The simulation training program for delirium assessment is a 7-day training program led by three psychiatrists. Evaluators will first view three standard interview videos and then use 3D-CAM and CAM-S to score the content described in the video to assess the presence and degree of delirium. Scores will then be compared with the video’s “gold standard” score to evaluate the assessor’s mastery of the delirium assessment. During the examination phase, the delirium assessment team will be divided into three groups, each consisting of two assessors and a psychiatrist. The delirium assessor must perform a simulated assessment and scoring of delirious and non-delirious patients using 3D-CAM and CAM-S. The assessor must agree with the psychiatrist on the presence or absence of all delirium features for at least three patients. During the examination phase, the assessor must demonstrate competence in delirium assessment and scoring, and the diagnosis of delirium must be in 100% agreement with the psychiatrist to be considered a pass. The training process will be repeated every month during the study to establish the assessor’s ability to score delirium reliably.

### Outcomes

2.11

#### Primary outcome

2.11.1

The primary outcome is the incidence of POD within 3 days of surgery. The initial evaluation of delirium will begin at least 6 h after surgery followed by 2 assessments daily (800–1,000 and 1,600–1,800) for the first 3 days after surgery, with an interval of at least 6 h between evaluations. Delirium will be assessed using the Chinese version of 3D-CAM (Marcantonio et al., 2014) in addition to medical records over the previous 24 h, nursing records, and discussions with family members.

The 3D-CAM identifies delirium through a diagnostic algorithm based on the four essential features of delirium: (A) acute changes or fluctuations in mental status; (B) inattention; (C) disorganized thinking; and (D) altered level of consciousness. Diagnosis of delirium requires criteria A and B and either or both of criteria C and D. The 3D-CAM has a high sensitivity (84–99%) and specificity (90–97%). If the subject is discharged or dies within 3 days, the last delirium assessment will be considered the replacement for any missing data.

#### Secondary outcomes

2.11.2

Number of POD episodes. One positive 3D-CAM assessment can be diagnosed as POD. Two consecutive negative 3D-CAM assessments were considered a transition from POD to non-POD status.The onset time and duration of delirium. The onset time of delirium is defined as the time from the subject being transferred back to the surgical ward to the first diagnosis of delirium. The duration of delirium is defined as the time elapsed from the subject’s diagnosis of delirium to 2 negative 3D-CAM assessments. The maximum duration of delirium will be recorded in patients with multiple delirium episodes.Delirium severity score. Patients with established delirium will also be assessed for delirium severity using the CAM-S (Inouye et al., 2014), with daily maximum scores recorded. The CAM-S scale has 4 items with a total score of 7 points. Symptom severity can be classified as absent (0), mild (1), or marked (2). The total score of 0 is normal, 1 is mild delirium, 3–5 is moderate delirium, and 6–7 is severe delirium.Subtypes of delirium. Delirium can be divided into three motoric subtypes according to its clinical manifestations: hyperactive, hypoactive, and mixed. The Richmond Agitation-Sedation Scales (RASS) classify delirium subtypes in patients with established delirium (Ely et al., 2003). Hyperactive delirium is defined as RASS that are consistently positive (+1 to +4); hypoactive delirium is defined as RASS that are consistently neutral or negative (−3 to 0); mixed delirium is defined when some RASS are positive (+1 to +4) and some are neutral or negative (−3 to 0).Pain scores at rest and exercise. Assessments will be performed using the NRS at 8:00–10:00 on postoperative days 1–3, during physical therapy on postoperative days 1–3, and at 16:00–18:00 on postoperative days 1–3. Resting is defined as the subject being in a quiet supine position, and exercise is defined as the subject lifting the affected limb at least 5 times to a height of at least 30 cm.Opioid consumption. Opioid consumption will be assessed on postoperative day 1, postoperative day 2, and overall. Opioid consumption, including PCIA and rescue analgesics, will be converted to a “morphine equivalent dose” for analysis.The time of first analgesia pump compression within 24 h of surgery (defined as the time elapsed from the start of the analgesia pump to its first compression).Post-operative sleep quality: The NRS will be used to assess the subject’s sleep quality on postoperative days 1–3 (on an 11-point scale where 0 = best sleep and 10 = worst sleep).Preoperative baseline and 3 days postoperative Timed Up and Go test. The Timed Up and Go test is the time it takes to get up from a standard-height armchair, walk three meters forward, walk back to the chair, and sit down.The active range of motion of the affected knee or hip at baseline and 3 days after surgery. The active range of motion is defined as the range from neutral (0°) to maximum flexion.BI score at baseline and 3 days after surgery.Time to discharge criteria, which include the subject being able to walk independently from their bed to the bathroom and along a hallway without the aid of a walker.Length of hospital stay. It is defined as the time elapsed from the day of the subject’s procedure to discharge.

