### Data collection

2.14

Data will be collected via face-to-face interviews with subjects and relatives or extracted from the HIS (Table 2).

**Table 2 tab2:** Enrollment schedule, interventions, and assessments.

Outcome measure	Visit 1	Visit 2	Visit3	Visit4	Visit 5	Visit 6	Visit 7	Visit 8
Time	Day of admission	1 day pre-surgery	During operation	6 h post-operative	1 d post-operative	2 d post-operative	3 d post-operative	Hospital discharge
Eligibility screening	X		–	–	–	–	–	–
Informed consent	X		–	–	–	–	–	–
Demographic characteristics	–	X	–	–	–	–	–	–
Baseline measures	–	X	X	–	–	–	–	–
Randomization	X	–	–	–	–	–	–	–
Intervention	Intraoperative S-ketamine will be infused continuously at 0.20 mg/kg/h for 1 h, followed by 0.01 mg/kg/h for 48 h							
Incidence of POD	–	–	–	X	X	X	X	–
Onset time of POD	–	–	–	X	X	X	X	–
Duration of POD	–	–	–	X	X	X	X	X
Severity of POD	–	–	–	X	X	X	X	–
Subtypes of POD	–	–	–	X	X	X	X	–
NRS	–	–	–	–	X	X	X	–
Opioid consumption	–	–	–	–	X	X	–	–
Pump compression	Within 24 h of surgery							
Clinical outcomes	–	X	–	–	–	–	X	–
Length of stay	–	–	–	–	–	–	–	X
Safety outcomes	Throughout the study period until discharge							

POD, postoperative delirium; NRS, number rating score.

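### Two differently worded rules end a delirium episode, and an episode positive at a day-3 test cannot close within the schedule, yet duration is analysed as complete

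*Protocol article*

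**What the plan says.** All references are to the protocol article.

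- **Start of an episode (2.11.2):** "One positive 3D-CAM assessment can be diagnosed as POD".
- **End of an episode (2.11.2, number of episodes):** "Two consecutive negative 3D-CAM assessments were considered a transition from POD to non-POD status".
- **End of the duration clock (2.11.2, onset and duration):** time runs from the "diagnosis of delirium to 2 negative 3D-CAM assessments". The word consecutive is absent.
- **More than one episode (2.11.2):** "The maximum duration of delirium will be recorded in patients with multiple delirium episodes".
- **Test schedule (2.11.1):** the first test comes no earlier than 6 h after the operation, and the later ones are set out as "followed by 2 assessments daily (800–1,000 and 1,600–1,800) for the first 3 days after surgery".
- **Early discharge or death (2.11.1):** the last assessment stands in for the missing ones.
- **Table 2 (2.14):** the row "Duration of POD" is marked at Visits 4 to 7 and also at Visit 8, hospital discharge. The rows for incidence, onset, severity and subtype stop at Visit 7.
- **Analysis (2.16):** duration is listed with the quantitative outcomes, for a Mann-Whitney test and a Hodges-Lehmann interval. Only time to first pump compression is handled as survival data. Secondary outcomes are exploratory and use the per-protocol set.

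**The concern.** A duration needs one agreed end point, and the observation period must be long enough to reach it. Here the end point is worded in two ways, and testing stops on a fixed day whether or not the patient has recovered. An episode still running at the last test has a known minimum length but no known end, so it is right-censored. A rank test that takes such a value as final, or that drops it, mishandles the episodes that start late or last long. Those include the ones a treatment effect on duration should shorten. The article fixes the definition, the schedule and the test but gives no rule for an open episode. A later analysis plan could add a censoring rule, but it could not recover tests that were never scheduled.

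**Working it through.** The plan gives no figure of its own on this point, so there is none to reproduce. The check is an enumeration.

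**Step 1. Number of tests (2.11.1).** One from 6 h, plus 2 per day × 3 days = 7: 6 h, D1 am, D1 pm, D2 am, D2 pm, D3 am, D3 pm.

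**Step 2. Tests left after the last positive (7 minus its position).**

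| Last positive | Tests left | Two consecutive negatives possible? |
|---|---|---|
| 6 h | 6 | yes |
| D1 am | 5 | yes |
| D1 pm | 4 | yes |
| D2 am | 3 | yes |
| D2 pm | 2 | yes, both day-3 tests |
| D3 am | 1 | no |
| D3 pm | 0 | no |

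The cut-off is therefore a positive at either day-3 test. A patient discharged or dying earlier with a positive last test is in the same position: carrying that result forward never produces a negative.

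**Step 3. Do the two end rules differ?** Take + − + − − − −. Under the consecutive rule the episode ends at D2 pm (negatives at D2 am and D2 pm). Under the literal duration rule it ends at D2 am (negatives at D1 am and D2 am). Over all 2^7 − 1 = 127 patterns with at least one positive, the two rules give different episode results in 43. These are counts of patterns, not probabilities.

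**Step 4. Open episodes by pattern.** Under the consecutive rule a pattern closes only if both day-3 tests are negative. That leaves 2^5 − 1 = 31 closed patterns and 127 − 31 = 96 open ones. Again this is a count of patterns and says nothing about frequency in patients.

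**Step 5. Size under a stated assumption.** The documents give no time course of onset. Suppose onset is equally likely at each of the 7 tests and an episode is positive at L tests in a row. It stays open if its last positive would fall at test 6 or later, which happens for L + 1 of the 7 starting positions.

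- L = 1: 2/7 = 29%
- L = 2: 3/7 = 43%
- L = 3: 4/7 = 57%

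If instead every onset fell at the first three tests, a three-test episode would have its last positive no later than test 5, and none would stay open. For episodes of one to three tests, the range across these two assumptions is 0 to 4/7.

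**Step 6. Number of cases.** Section 2.3 assumes 17% and 7%.

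- With 186 per group: 31.6 + 13.0 = 44.6 cases.
- With 166 per group (after the plan's 10% loss, closer to what a per-protocol set might hold): 28.2 + 11.6 = 39.8 cases.

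Under even onset, the open episodes among 39.8 cases would number 11.4, 17.1 or 22.8 for L = 1, 2 or 3. Among 44.6 cases they would number 12.7, 19.1 or 25.5.

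**The case against.** The strongest reply has three parts.

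1. **The two rules are one rule.** The duration phrase may be shorthand for the consecutive rule a few sentences before it, since the sentence on multiple episodes relies on that rule. This is quite likely what was meant, and then one missing word is the whole of the first fault. The text does not say so, however, and alternating results are plausible because fluctuation is itself one of the diagnostic features in 2.11.1.
2. **Table 2 provides for follow-up.** Duration is the only delirium row marked at discharge, which suggests that open episodes are meant to be followed. This stands in part: some late episodes might be closed that way. But the article sets no 3D-CAM after day 3, so how the end would be measured is not stated.
3. **The outcome is exploratory.** This stands, and it limits the weight of the point.

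A reader might also infer more than the documents support:

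- *That an episode positive on the evening of day 2 can no longer close.* It can, on the two day-3 tests: of the 64 patterns positive at D2 pm, the 2^4 = 16 that are negative at both day-3 tests close under the consecutive rule.
- *That neither rule can be met after a day-3 positive.* The literal duration rule can: D2 am +, D2 pm −, D3 am +, D3 pm − has two negatives by D3 pm.
- *That many durations are undefined.* No time course is given, and Step 5 allows anything from none to more than half.
- *That the comparison is biased in a known direction.* Both groups have the same schedule, and no direction can be derived. The share of open episodes would differ by group if treatment shifted onset or length, but the documents do not show that.
- *That taking the longest episode discards recurrent delirium.* The number of episodes is a separate secondary outcome.

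**Conclusion.** The point holds in a limited form. The two end rules differ in wording and, read literally, can give different durations. Under the consecutive rule, an episode positive at the 6th or 7th test, or at the last test before early discharge or death, has no end within the stated schedule. No rule covers it, and the planned analysis takes duration as complete, so the latest and longest episodes are undefined or truncated. The share affected cannot be taken from the documents. The 2/7 to 4/7 figures rest on even onset, runs of one to three positive tests and no 3D-CAM after day 3. Early onset or real follow-up to discharge would lower them. With only about 40 to 45 expected cases, even a modest share would matter to this comparison. The primary outcome is not touched.

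**What to change.** - **Section 2.11.2:** require two consecutive negative tests in both the episode sentence and the duration sentence, and say whether the clock stops at the first or the second of them.
- **Section 2.16:** treat an episode open at the last test as right-censored, and analyse duration by Kaplan-Meier and log-rank, as already planned for time to first pump compression. If the full protocol provides 3D-CAM tests until discharge, say so and censor at the last of those instead.
- **Alternative, as a supporting measure:** report the number of the 7 scheduled tests that are positive, compared by Mann-Whitney. It needs no end rule and uses tests already scheduled.

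The cost is small: a few words in 2.11.2, a changed analysis for one exploratory outcome, and no new tests. There are two drawbacks. The survival analysis would report something other than a Hodges-Lehmann shift and would treat censoring at discharge or death as uninformative. The count, if taken over all patients, would be zero for about 88% of them at the design rates (1 − (0.17 + 0.07)/2), so it would largely repeat the primary comparison. Its analysis set would also have to be stated, because 2.16 restricts secondary outcomes to the per-protocol set.

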
#### Safety outcomes

2.11.3

Patients will be monitored for adverse events for 24 h after surgery or until the resolution of an adverse event. Tachycardia is a heart rate greater than 100 beats per minute and bradycardia is less than 45 beats per minute. Hypertension is a systolic blood pressure greater than 180 mmHg or a greater than 20% increase from baseline, and hypotension is systolic blood pressure less than 90 mmHg or a greater than 20% decrease from baseline. Hypoxemia is a blood oxygen saturation of less than 95% with supplemental oxygen and a pulse oxygen saturation of less than 90% without supplemental oxygen. Unplanned transfer to ICU. S-ketamine-related psychiatric complications include dreaminess, nightmares, dizziness, and hallucinations. Early postoperative nausea and vomiting refers to nausea and vomiting within 2 h of surgery. A non-delirious postoperative complication is a new illness other than postoperative delirium requiring therapeutic intervention within 30 days of surgery.

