
### Interventions

2.9

Subjects in the intervention group will receive an intravenous infusion of S-ketamine (Jiangsu Heng Rui Medicine Co., Ltd., Jiangsu, China) following a standard dilution protocol (40 mg S-ketamine with 0.9% normal saline to 20 mL, 2.0 mg/mL). The infusion rate of S-ketamine will be 0.1 mL/kg/h (0.20 mg/kg/h), the infusion mode will be constant speed pumping, and the infusion time will be 1 h. In the control group, subjects will receive 0.9% saline at 0.1 mL/kg/h for 1 h at a constant rate infusion.

All subjects will be transferred to the PACU after surgery. The PCIA device will be connected and started. In the intervention group, the PCIA device will be filled with 1.0 mg/kg S-ketamine, 50 μg sufentanil (Yichang Renfu Pharmaceutical Co., Ltd., Yichang, Hubei, China), 6 mg butorphanol tartrate (Jiangsu Heng Rui Medicine Co., Ltd., Jiangsu, China) and 8 mg ondansetron, diluted to 100 mL with normal saline. In the control group, the PCIA device will not contain S-ketamine. The background dose will be 1 mL/h, the single bolus dose 2 mL, the lockout time 15 min, and the maximum infusion rate 8 mL/h.

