The choice of S-ketamine dose and mode of administration was based on published clinical trials and drug manufacturer instructions. S-ketamine is twice as potent in analgesia as ketamine, and the same anesthetic effect can be achieved with a dose of 1/2 ketamine. A subanesthetic dose of S-ketamine (0.25 mg/kg) was often selected by the investigator for the prevention of POD or perioperative neurocognitive dysfunction (Wei et al., 2022; Han et al., 2023; Ma et al., 2023). However, we need to be clear that a dose of 1/2 ketamine may not be equivalent to the dose at which S-ketamine exerts neuroprotective effects, and that relatively high doses of S-ketamine are more prone to adverse events and potential safety concerns (McIntyre et al., 2021). Subjects will receive intraspinal anesthesia rather than general anesthesia in this study, which avoids the influence of other anesthetic drugs on the neuroprotective effects of S-ketamine. In addition, elderly patients with preoperative dementia, depression, and multiple comorbidities will be included, making the dose of S-ketamine received in the intervention group more conservative. Our previous study found that subjects receiving 0.3 mg/kg/h S-ketamine had hallucinations and dreaminess, although this dose was subanesthetic (Zhu et al., 2023). Therefore, we will use a smaller subanesthetic dose of S-ketamine 0.2 mg/kg infused over 1 h in this trial. In antidepressant therapy, the short-term efficacy of intravenous ketamine necessitates repeated dosing in most cases to maintain therapeutic benefit. Therefore, the intervention group will receive an intravenous infusion of 0.010 mg/kg/h for 48 h via the PCIA device after surgery, a dose with fewer psychiatric side effects and maintaining the need for analgesia.

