### Adverse events reporting

2.13

Adverse events (AE) refer to all untoward medical events that occur after the subject receives the investigational product. These include symptoms, signs, diseases, or laboratory abnormalities but may not necessarily have a causal relationship with the investigational product. The investigator should record and report all AE that are directly observed or spontaneously written by the subject in concise language. In addition, subjects should be asked about AE from the beginning to the end of the trial. AE should be recorded on the designated Adverse Event Form. The severity of AE will be judged according to standard adverse reaction evaluation criteria. All AE will be handled according to the standard operating procedures for handling adverse reactions that were developed by the clinical trial center. The AE record form shall be truthfully filled in, including the occurrence time, severity, duration, measures taken, and outcome of the AE.

A serious adverse event (SAE) refers to death or a life-threatening event, permanent or severe disability or loss of function, hospitalization or prolongation of hospitalization, a congenital anomaly or disability, or any other important medical events experienced by the subject after receiving the investigational product. Any subject with SAE should be withdrawn from the trial, and the investigator should actively treat the subject with SAE. The investigator must also complete the SAE Report Form in as much detail as possible, and sign and date it. The investigator should report the SAE to the Principal Investigator ([name]) and the Ethics Committee of Qingdao University within 24 h of being informed of the SAE.

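### The safety sections give conflicting windows, the shortest ending midway through the 48 h postoperative infusion, and the 30-day complication outcome has no scheduled collection after discharge

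*Protocol article*

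**What the plan says.** Four places in the protocol article bear on when safety events are counted.

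- Section 2.11.3 (Safety outcomes) opens with "Patients will be monitored for adverse events for 24 h after surgery or until the resolution of an adverse event". It then defines the heart-rate, blood-pressure and oxygenation events, unplanned ICU transfer and the S-ketamine-related psychiatric complications. None of these has a window of its own.
- Section 2.13 (Adverse events reporting) says that "subjects should be asked about AE from the beginning to the end of the trial".
- Table 2 in section 2.14 (Data collection) gives the timing of the safety outcomes as "Throughout the study period until discharge". Its last visit is hospital discharge.
- Section 2.11.3 also defines a non-delirium complication as a new illness "requiring therapeutic intervention within 30 days of surgery".

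On exposure, section 2.9 (Interventions) states that "the intervention group will receive an intravenous infusion of 0.010 mg/kg/h for 48 h via the PCIA device after surgery", and Table 2 repeats the 48 h. Section 2.14.4 lists the safety data without a window. Section 2.16 defines the Safety Analysis Set but no period over which its events are counted.

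**The concern.** A safety rate needs a defined period at risk. Here three periods are stated for adverse events, and the section that defines the outcomes gives the shortest. That period ends while study drug is still running. The events most relevant to S-ketamine (dreaminess, nightmares, dizziness, hallucinations) are named safety outcomes. Section 2.9 defends the postoperative dose partly because it has fewer psychiatric side effects, and it reports hallucinations and dreaminess at a higher infusion rate in the team's own earlier study. A 24 h cut-off would leave that expectation unexamined on the second day, in a population that may include patients with dementia.

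If the window is settled only after data are in hand, the reported rates depend on that choice. The complication outcome has a related problem: its name promises 30 days, but the schedule stops at discharge.

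**Working it through.** **1. Reproduce the plan's infusion.** From section 2.9: "the PCIA device will be filled with 1.0 mg/kg S-ketamine", made up to 100 mL, and "The background dose will be 1 mL/h, the single bolus dose 2 mL, the lockout time 15 min, and the maximum infusion rate 8 mL/h".

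- Background rate: 1.0 mg/kg ÷ 100 mL × 1 mL/h = 0.010 mg/kg/h, as stated.
- Volume over 48 h: 48 h × 1 mL/h = 48 mL of the 100 mL.

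The stated rate and duration therefore agree with the pump settings and with Table 2 ("Intraoperative S-ketamine will be infused continuously at 0.20 mg/kg/h for 1 h, followed by 0.01 mg/kg/h for 48 h"). The 48 h is the actual plan, not a slip in one sentence.

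**2. Apply the 24 h sentence literally.** Assume that the pump starts at about the end of surgery.

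- Infusion hours outside the window: (48 − 24) ÷ 48 = 50%.
- Background dose after 24 h: 0.010 × 24 = 0.24 mg/kg.
- Whole postoperative background dose: 0.010 × 48 = 0.48 mg/kg.
- Intraoperative dose: 0.20 mg/kg/h × 1 h = 0.20 mg/kg.
- Share of total planned dose after 24 h: 0.24 ÷ (0.48 + 0.20) = 0.24 ÷ 0.68 = 35%.

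**3. Allow for patient boluses.** Assume a constant total draw of r mL/h and no refill. The pump then lasts min(48, 100/r) hours.

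| Total draw r | Pump lasts | Infusion hours after 24 h |
|---|---|---|
| up to 100/48 = 2.08 mL/h | 48 h | 50% |
| 3 mL/h | 33.3 h | 1 − 24/33.3 = 28% |
| 4 mL/h | 25 h | 1 − 24/25 = 4% |
| 8 mL/h (the ceiling) | 12.5 h | 0% |

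So 50% is the figure for low to moderate bolus use, and it falls with heavy use.

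**4. Apply the other two windows.** With collection until discharge (Table 2), or enquiry to the end of the trial (section 2.13), the uncovered part of the infusion is 0 h for a patient who is in hospital throughout it.

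**5. The 30-day outcome.** The time without scheduled contact is 30 days minus length of stay. The article gives no expected stay. Assuming 3 to 10 days, it is 30 − 3 = 27 down to 30 − 10 = 20 of the 30 days. Section 2.14 names interviews in person with patients and relatives, and the hospital information system, as the data sources. It names no visit or call after discharge.

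**The case against.** The strongest reply is that the longer windows are in the text. Section 2.13 requires enquiry beyond 24 h and the recording of all observed or reported events, and Table 2 runs to discharge. Section 2.12 sets continuous ward monitoring at a minimum of 24 h, so the sentence in 2.11.3, which stands just before the vital-sign definitions, may describe that minimum rather than a cut-off for counting. This stands as a possible reading. It shows that loss of data is not certain, but the article does not say it, and 2.11.3 is worded as a limit on adverse-event monitoring in general. The clause about resolution does not clearly admit events that begin after 24 h.

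Three stronger readings are tempting, and the documents do not support them.

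- A reader might infer that the safety tables will miss half of the infusion. That holds only if the 24 h sentence governs.
- A reader might infer that half of the events would be lost. That needs a constant event rate. The intraoperative hour runs at 20 times the later background rate (0.20 ÷ 0.01), so events may cluster early.
- A reader might infer that complications after discharge are not collected at all, or are truncated differently by arm. The hospital information system could hold events treated at the same hospital. The article gives neither a length of stay nor an expected effect on it, so a difference between arms is conjecture.

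It is also fair to say that an article may leave the method of a 30-day contact to the full protocol. The mismatch between 30 days and until discharge is nevertheless on the page.

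**Conclusion.** The point holds as an internal contradiction with a conditional consequence. The three adverse-event windows cannot all define the same counts. If the 24 h sentence is used, 24 of 48 postoperative infusion hours lie outside it (50% of hours, about 35% of the planned dose at background rate). New psychiatric or haemodynamic events on the second day may then not be counted. If section 2.13 or Table 2 is used, nothing of the in-hospital infusion is missed. The percentages assume that the pump starts at the end of surgery and that bolus use does not empty it before 48 h.

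The complication outcome is defined to 30 days but has no scheduled collection after discharge under any reading. Capture for the remaining days (20 to 27 for an assumed stay of 3 to 10 days) would be incomplete rather than certainly absent.

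Severity is moderate. The primary outcome, sample size and efficacy analysis are untouched, and any under-count would apply to both blinded arms.

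**What to change.** Reconcile sections 2.11.3 and 2.13 and Table 2 into one counting window for the safety outcomes. It should cover the whole study-drug infusion and run to discharge, as Table 2 already says. If the 24 h sentence is meant as a minimum period of ward monitoring, say so and separate it from the counting rule. Say also how the vital-sign events are ascertained after the first 24 h, so that their rates can be interpreted. Record the psychiatric symptoms at the twice-daily delirium assessments that already run through day 3.

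For the non-delirium complications, either restate the outcome as complications until discharge, or keep 30 days and name the post-discharge source. That source would be the hospital information system, with an optional telephone call at day 30.

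The cost is protocol and eCRF wording, plus a few items at assessments that already take place. Only the optional call adds contact, at one per patient. Dose, infusion duration and clinical management are not touched.
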